**Data collection**

- HOME-BASED SCREENING ASSESSMENT (main team member(s) responsible: [name])

Researchers trained in assessment with older adults will visit potential participants selected through general practices and pre-screened with the SARC-F (i.e. evaluated by the research team as safe to proceed) in their own home to carry out screening for other exclusion/ inclusion criteria not assessed at pre-screening (e.g. milk allergies, participation in structured resistance exercise in the last month). Grip strength and walking speed will be measured to establish participants’ muscle strength and function status based on the established cut-offs^5^. An informed consent will be conducted before the assessments. Eligible individuals will be informed about the study procedure and their journey through the study (from randomisation to post-intervention assessment). Non-eligible individuals will be explained why they did not qualify for the study, thanked for their time, and will be informed about the possibility to participate in other studies led by [name] [name] (AGE Research Group).

This visit with the informed consent will last about 35 (maximum 40) minutes.

- HOME-BASED BASELINE ASSESSMENT: HEALTH AND FUNCTIONING PROFILE (main team member(s) responsible: [name])

Trained researchers will visit 30 participants enrolled in the study in their own home to conduct in depth interview and baseline assessments of the following domains:

1. Sociodemographic profile: age; sex; marital status; education; social class, and multiple index of deprivation
2. General health and functioning: SF-12 Health Survey^29^; self-reported diseases diagnosed by a doctor; list of medication (prescribed and over-the-counter); Mini Mental State Examination; Geriatric Depression Scale (15-item version) and Barthel Index^30^ (Activities of Daily Living); blood pressure (systolic and diastolic)
3. Dietary intake: 24-hr dietary recall (Intake24 (https://intake24.co.uk/) multi-pass, computerised 24-hr recall supported by the Newcastle University)
4. Appetite assessment: a 4-item Simplified Nutritional Appetite Questionnaire^34^
5. Self-reported physical activity: questionnaire assessing the frequency and duration of low intensity, moderate intensity and vigorous intensity physical activity, as assessed in the Newcastle 85+ study^35^
6. Anthropometry: demi-span (sex-specific height calculation), waist, hip and calf circumference
7. Muscle strength: maximum grip strength measured 3 times in each arm
8. Physical performance: Short Physical Performance Battery^26^ (balance, 4m-gait speed, 5-chair stands)
9. Muscle mass (body composition), as measured by Bioelectric Impedance Analysis (BIA; Tanita MC-780MA Body Composition Analyzer).

Baseline assessments of blood pressure and muscle mass (body composition) will be conducted at the intervention site (The Parks, Contours gym) before the first RE session, and dietary intake and appetite will be assessed during the post-exercise recovery period. Body analyser will be parts tested by the NTGH.

Detailed health and functioning profile will involve minimal risk and inconvenience to participants and will be conducted under 70 minutes (including verification of the informed consent and excluding assessments done at The Parks).

- INTERVENTION: MILK/ CONTROL DRINK + RESISTANCE EXERCISE (main team member(s) responsible: certified exercised physiologist and [name])

Thirty participants will be randomized into three groups (10 each; 5 men and 5 women):

1. ‘whole milk + RE’;
2. ‘skimmed milk + RE’, and
3. ‘control drink’ (juice supplemented with carbohydrates) + RE’.

Resistance exercise programme

RE will be conducted over 6 weeks (twice a week on two non-consecutive days) at The Parks, Contours gym & fitness suite, North Shields, North Tyneside Council in a small group of 2-3 participants, and will be supervised by a trained and experienced exercise physiologist. Participants will be advised to resume their usual diet, and to have their regular breakfast before the intervention. Four sets of 8-12 repetitions (upper and lower body) exercises at the sub-maximal level of effort (70-79% 1-repetition maximum) will be performed after a short warm-up exercise (e.g. 5 minutes of stretching exercises, walking or stationary cycling)^36,37^. Each set of RE will be followed by 1-2 minute of resting period, and a rest of 4 seconds between repetitions^36^. Each participant will receive a booklet with diagrams and short instructions of exercise programme (RE booklet). To increase their engagement in exercise, each participant will have the opportunity to record in the RE booklet how many repetitions and how much weight for each set of exercise they have completed and lifted.

Exercise intensity, volume, frequency and duration have been determined based on the recent literature^36-38^, and the American College of Sports Medicine (ACSM) recommendations for older adults^37^. Details about the RE programme over 6 weeks are outlined in the RE protocol (MIlkMAN_Resistance Exercise Protocol_v.1-20-07-18). The complete RE session will be finalised within 1 hour, except the first RE session, which will last 1 hour and 30 to 40 minutes and include a short induction programme at the gym detailed below. Blood pressure and heart rate will be measured pre and post each RE session. Blood pressure classification and cut-offs for the blood pressure change pre and post-RE will be based on the guidelines provided by the American College of Cardiology/American Heart Association Task Force^39^ and on the published literature^40-42^. For older adults aged 65 and over blood pressure of 130/80 mmHg is considered as optimal^39^. Exercise physiologist will record changes in blood pressure and heart rate pre and post each RE session. If participant’s blood pressure approaches the exclusion criteria for the study (>160/100 mmHg for hypertension and <100mmHg systolic for hypotension) before exercise, the Chief Investigator (a consultant physician) will be notified and consulted. Changes that are regarded to be adverse events will be recorded and reported to the Chief Investigator ([name]) for evaluation and further adverse events reporting (described below). Any other health risks will be closely monitored by exercise physiologist. Post-exercise differential ratings of perceived exertion (RPE) ~ 10 minutes after the completion of exercise will be assessed using the CR100® scale^43^ (Appendix 2). The scale offers finely graded numerical range of 0-100 arbitrary units (AU) with several verbal anchors next to the scale corresponding to whole numbers (0 ‘nothing at all’; 12 ‘easy’; 22 ‘moderate’; 35 ‘somewhat hard’; 50 ‘hard’; 70 ‘very hard’; 100 ‘maximal’). Participants will be asked to self-asses their level of perceived exertion for the overall session, and upper-body and lower-body muscles. Muscle soreness will be assessed with a simple visual analogue scale (Appendix 3) ~40-45 minutes after each RE session. Additionally, each participant will be called at home in the evening (up to 6-7 hours post-RE) to evaluate his/ her muscle soreness using the same visual analogue scale.

During the intervention, participants will be advised to resume their regular level of physical activity and lifestyle habits and not to participate in any other activities provided with the gym membership during the intervention.

Facility

The supervised RE programme will be conducted in the community at a sports/ recreation centre (e.g. The Parks, Contours gym & fitness suite, North Shields, North Tyneside Council). The RE equipment for upper and lower body exercises will be provided by the centre, and will be used as a part of free monthly membership (£60 for 6 weeks/participant paid by the study grant). Each participant will complete a short medical questionnaire provided by the gym, sign the Contours gym membership terms and conditions agreement (<https://my.northtyneside.gov.uk/sites/default/files/web-page-related-files/CONTOURS%20MEMBERSHIP%20TERMS%20AND%20CONDITIONS%202016.pdf>), and undergo a short induction programme

(<https://my.northtyneside.gov.uk/sites/default/files/web-page-related-files/Contours%20Gym%20Inductions.pdf>) before the commencement of the first intervention session. The Contours instructor will conduct only the first part of the induction programme and explain the use of gym facilities and resistance machines to each participant (contact person: [name], GP Referral Instructor, Environment, Housing, Leisure, North Tyneside Council; [[contact]](mailto:[contact]) ). A private room with a fridge (parts tested) will be provided at the Parks for the participants’ recovery and milk drinking (500ml) during the duration of the intervention.

Milk and control drink intake

Milk / control drink will be consumed as a bolus intake of 500ml under the supervision of a researcher immediately after exercise over 40-50 minutes during the recovery period (or longer if needed). Participants will be advised to resume their usual diet. Second dose of 500ml will be consumed at participants’ home over the next 4-5 hours. All drinks consumed at home will be clearly labelled as either ‘MIlkMAN study milk’ or ‘MIlkMAN study juice’. Second dose of 500ml can be consumed with other foods as a part of their usual diet (e.g. tea, cereal, mushed potatoes, etc.). Participants will be contacted by phone in the evening to check for muscle soreness and compliance with milk/ control drink consumption. Each participant will be provided with a plastic measuring jug (500ml) and a log sheet to measure and record milk/control drink consumption at home and to report it back to a researcher conducting the phone call.

On average, 500ml milk contains ~20g of protein needed to stimulate muscle protein synthesis above stimulation provided by RE. Whole (cow) milk (nutritional estimates of 22 UK samples during winter and summer) provides 66 kcal/100g of energy^44^. Fresh milk will be provided by Arla® (Nutrition Specialist: [name] at Arla Foods). Arla Cravendale® whole milk contains 3.6g fat, 3.4g protein, and 4.7g of carbohydrates per 100g of milk. Arla Cravendale® skimmed milk contains 0.3g fat, 3.6g protein, and 4.9g of carbohydrate per 100g of milk. Energy of control drink (cranberry juice; Ocean Spray Classic) will be balanced to match whole milk energy content and supplemented with maltodextrin (e.g. cranberry juice (45kcal/100g of energy^44^) will be supplemented with 6.05g of maltodextrin (3.8kcal/g) per 100g of juice; 1tsp = 15kcal; 30.25g for 500ml of juice).

Milk and control drink storage and handling

Milk (whole and skimmed) will be provided by Arla® (contact person: [name], Senior Nutrition Specialist, Arla Foods, Aarhus, Denmark; [contact]) in packs of either 500ml or 1 litre on a bi-weekly basis through a local distributor (Tesco or Sainsbury’s), and refrigerated at the Campus for Ageing and Vitality, Newcastle University for a long-term storage (parts tested fridge with a lock). Arla Cravendale® milk stays fresh for 21 days if left unopened. Control drink (cranberry juice) will be bought fresh weekly (Tesco) and refrigerated in a similar fashion. Control drink will be supplemented with maltodextrin at the day of intervention by a research team member. During the intervention period of the study, a researcher not involved in exercise intervention will transport milk/ control drink in cooler boxes to The Parks on daily basis. At The Parks, a fridge (parts tested) will be provided in a designated recovery room for a short-term storage of milk/ control drink.

The total time needed to complete the first visit at The Parks is about 2 and half hours (gym induction programme, assessments, intervention and recovery). This first visit will include blood pressure, body composition, diet and appetite assessment as a part of baseline assessment. The total time needed to complete the remaining RE + drink intake sessions (including recovery period) is 1 hour and 45 minutes. For participants who need more rest, additional times will be provided. The last (12th) visit at The Parks will include body composition, blood pressure, diet and appetite assessment after exercise as a part of post-intervention assessment and will last 2 hours and 10 minutes.

Individual transport will be provided to transport participants to The Parks and back home.

Those who prefer to use public or personal transport or to walk will be reimbursed for their fare.

- HOME-BASED POST-INTERVENTION ASSESSMENT (main team member(s) responsible: [name])

A post-intervention visit, in the participants own home, will be arranged after 6 weeks of intervention to assess the following domains:

1. Physical performance: Short Physical Performance Battery (balance, 4m-gait speed, 5-chair stands)
2. Muscle strength: maximum strength test (grip strength, GS; Jamar hand-held 5030J1 dynamometer)
3. Muscle mass: Bioelectric Impedance Analysis (BIA; Tanita MC-780MA Body Composition Analyzer)
4. Dietary intake: 24-hr dietary recall (Intake24 (https://intake24.co.uk/) multi-pass, computerised 24-hr recall supported by the Newcastle University)
5. Appetite assessment: a 4-item Simplified Nutritional Appetite Questionnaire
6. General health and functioning: Self-reported quality of life: SF-12; Activities of daily living: Barthel Index; blood pressure (systolic and diastolic)

Participants’ feedback will be collected at the end of follow-up assessment using a combination of structured multiple-response and standardised open-ended questions to explore the following themes:

1. Attitudes and barriers of 2 × 500ml milk intake post-exercise (e.g. volume of liquid, taste, etc.)
2. Their opinion about milk as a functional food for muscle strength/ function
3. Appetite changes, changes in habitual diet because of milk/ control drink intake
4. What they liked and disliked about the study (intervention).

The follow-up visit will be completed within 50 minutes.

Muscle mass (body composition), appetite assessment (a 4-item Simplified Nutritional Appetite Questionnaire), dietary intake (24-hr dietary recall) and blood pressure will be assessed at the last (12^th^) intervention visit during the 45 minutes recovery period at The Parks.

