**Hypotheses**

1. Consumption of whole milk (2 × 500ml; 2 × ~20g protein) after a RE session twice a week over the period of 6 weeks post-randomisation is feasible as an intervention in older adults (aged ≥65) who may be at risk of sarcopenia.
2. The intervention is acceptable with good compliance, low attrition, and no adverse health effects, including appetite suppression, negative dietary changes, muscle damage and soreness.

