# Primary and secondary outcomes of the study

Primary outcome measures

1. Feasibility and acceptability of the intervention (Time frame: 6 weeks post-randomisation and baseline assessment).
2. Measures to include: applicability, dosage and duration of the intervention, compliance, attrition, and adverse health effects such as appetite suppression, dietary changes and muscle soreness (Time frame: 6 weeks post-intervention).

Secondary outcome measures for exploratory analyses

1. Difference in physical performance measures: Short Physical Performance Battery^26^ (balance, 4m-gait speed, 5-chair stands) (Time frame: at baseline and after 6 weeks of intervention).
2. Difference in muscle strength measure: maximum strength test^27^ (grip strength, GS; Jamar hand-held 5030J1 dynamometer) (Time frame: at baseline and after 6 weeks of intervention).
3. Difference in muscle mass measure: Bioelectric Impedance Analysis (BIA; Tanita MC-780MA Body Composition Analyzer) (Time frame: at baseline and after 6 weeks of intervention)^28^.
4. Difference in self-reported quality of life measure: SF-12 (Time frame: at baseline and after 6 weeks of intervention)^29^.
5. Difference in activities of daily living measure: Barthel Index^30^.

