**Exclusion criteria**

1. Lacks capacity to consent—capacity is essential given the nature and demands of the research and the aim to gain participant feedback of the research experience
2. Self-reported lactose intolerance or milk allergies
3. Dislikes milk
4. Unable to understand instructions for muscle strength and function assessments in English or unwilling to participate in protocol when explained
5. Dislikes gym exercise with equipment
6. Doctor diagnosed diabetes I and II
7. Doctor diagnosed impaired renal function (estimated glomerular filtration rate <30ml/min/1.73m^2^)
8. Doctor diagnosed liver function impairment (e.g. viral hepatitis, alcoholic hepatitis, liver cirrhosis, biliary obstruction, non-alcoholic fatty liver disease, ischemic liver injury)
9. Significant respiratory disease (e.g. COPD, severe asthma, and bronchitis)
10. Doctor diagnosed gastrointestinal tract disease (e.g. gastritis, peptic ulceration, inflammatory bowel disease, gastric carcinoma, pancreas disease)
11. History of neuromuscular problems and all other co-morbidities that substantially interact with mobility and muscle metabolism (e.g. severe arthritis, rigidity, paralysis)
12. Pacemaker or severe heart failure or any other significant heart disease
13. Uncontrolled hypertension (160/100) and uncontrolled hypotension (<100 systolic)
14. Hip or knee replacement
15. An individual who the research team (i.e. exercise physiologist) evaluates as not suitable for the intervention because of safety reasons
16. BMI ≥30kg/m^2^
17. Unintentional weight loss ≥5kg for the last 3 months
18. Taking warfarin (because of possible interaction with control drink (cranberry juice))
19. Structured resistance exercise training and gym-based programme in last month
20. An individual who the General Practitioner feels it is inappropriate for the researchers to approach—the general practitioner has detailed knowledge of patients and may consider individual unsuitable for approach for reasons such as end stage terminal disease or safety risk such as any medical and physical conditions that preclude safe participation in an exercise programme.

Recruitment (main team member(s) responsible: [name])

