# Ethical considerations and risk and burden

As with all research involving human subjects the wellbeing and safeguarding of individuals is paramount.

All researchers who have direct contact with participants will have all of the necessary approvals in place to include research passport, health checks, employment contracts, disclosure and barring service checks and will be fully trained to undertake the examinations included within the study.

Interview and other data (e.g. bioelectrical impedance, dietary intake) will be pseudonymised using a unique identifier at the time of collection. For long term storage and analysis, pseudonymised data will be encrypted and compressed, and retrievable only by members of the core research team. All anonymised data will be securely stored within a fire-walled password protected domain. Only core team member responsible for data analysis can link pseudonymised data back to individual participants.

As stated above, this study will exclude individuals who do not have capacity to consent. Should an individual lose consent during the ‘active’ period of this study then the participant will be withdrawn at that point. Permission to retain data gathered before loss of capacity is included in the participant consent form.

It is very unlikely that participants will experience harm by taking part in this study. There is small risk of increased muscle soreness and discomfort after each exercise session that will be carefully monitored and recorded by a trained exercise physiologist. Participants will be assessed regularly for muscle soreness and any signs of excess discomfort and stress using visual analogues scale, and will be called at home after each intervention session in the evening (i.e. twice a week over 6 weeks of intervention). Muscle injury with the proposed RE programme is highly unlikely because each participant will exercise at the sub-maximal level of effort, and will be supervised by a trained and certified exercise physiologist. The Parks (Contours gym) has health and safety procedures and indemnity insurance covered through the gym membership in the case of adverse events related to the equipment and facility use (contact person: [name], Operational Manager, Indoor Sport and Leisure, North Tyneside Council; [[contact]](mailto:[contact]) ). Any change in blood pressure and heart rate pre and post-RE will be carefully monitored and recorded.

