**Appendix 3**

Visual analogue scale for muscle soreness

[figure not shown]

0 = no pain, 1-3 = mild pain, 4-6 = moderate pain; 7-10 = severe pain

**Instructions for participants** (explained to participants by a researcher)

- This is a Visual Analogue Scale. The scale describes the intensity of your pain, 0 meaning no pain at all, 1 to 3 meaning mild pain, 4-6 moderate pain, and 7-10 the worst pain.
- Assessment ~45 minutes after exercise: Which number on the scale describes the best your muscle soreness in your (i) arms and (ii) legs?
- *Assessment in the evening over the phone (6-7 hours after exercise)*: A researcher will call you in the evening after each visit to the Parks to ask you again about your muscle soreness in your arms and legs. Please use the visual analogue scale that we gave you to rate your muscle soreness in your (i) arms and (ii) legs.

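### Muscle soreness is never rated before exercise, so aches that participants already had can be counted as soreness from the intervention

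*Protocol*

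**What the plan says.** Under Data collection (Resistance exercise programme), the protocol fixes two soreness ratings per session. The first is during recovery: "Muscle soreness will be assessed with a simple visual analogue scale (Appendix 3) ~40-45 minutes after each RE session". The second is by telephone, when each participant is "called at home in the evening (up to 6-7 hours post-RE) to evaluate his/ her muscle soreness". Appendix 3 repeats these two times and no others, and words the item as "Which number on the scale describes the best your muscle soreness in your (i) arms and (ii) legs".

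Soreness carries weight in the plan. The primary outcome measures include "compliance, attrition, and adverse health effects such as appetite suppression, dietary changes and muscle soreness". Hypothesis 2 expects "no adverse health effects, including appetite suppression, negative dietary changes, muscle damage and soreness". The section on ethics and risk states the risk as a change: "There is small risk of increased muscle soreness and discomfort after each exercise session".

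Other measures do have an earlier value. For the exercise sessions, "Blood pressure and heart rate will be measured pre and post each RE session". Appetite and dietary intake, the other two adverse effects that the primary outcome names as examples, are assessed at baseline and after the intervention. The list of baseline assessments contains no rating of arm or leg soreness.

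**The concern.** Hypothesis 2 is about soreness that the intervention brings on. The Appendix 3 item asks how sore the arms and legs are now, without reference to cause or change. A participant who arrives with a mild ache and leaves with the same ache is recorded in the mild pain category.

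No comparison within the trial removes this. All three groups do resistance exercise, so no group shows the level of soreness without it. Randomised allocation balances existing aches between groups in expectation, but it does not correct the absolute level, and the absolute level is what an acceptability judgement uses.

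The consequence is an adverse-effect figure that may be too high, carried into the planning of the main study. A later analysis plan cannot repair this, because the missing value is never collected.

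**Working it through.** The protocol gives no numerical result on soreness to reproduce. The check is a count of planned ratings, a reading of what each can show, and an illustration on stated assumptions.

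**1. Planned ratings.** Inputs: two sessions a week for six weeks, so 12 sessions; two times per session, both after exercise; two regions, arms and legs.
- Per participant: 12 × 2 × 2 = 48.
- Over 30 participants: 48 × 30 = 1,440.
- Taken before exercise or at baseline: 0.

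**2. What a rating contains.** Let B be the background ache, R the soreness left by earlier sessions and S the soreness from today's session, and suppose that they add.
- Post-session score = B + R + S.
- Soreness due to the intervention = R + S.
- The excess is B, and nothing in the current schedule estimates B.

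**3. Illustration of the number affected.** The protocol gives no prevalence of background ache. Assume 10% to 40% of participants.
- 0.10 × 30 = 3, and 0.40 × 30 = 12.
- So 3 to 12 participants would score at least 1 on the 0–10 scale with no effect of the intervention.

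**4. Illustration of the shift in the mean.** Assume that 20% to 40% have an ache of 2 to 3 points that is stable over the six weeks. The shift in a region's mean is the proportion affected in that region × points.
- If all those affected have pain in both regions: 0.2 × 2 = 0.4 to 0.4 × 3 = 1.2 points.
- If each has pain in one region only, split evenly: half of that, 0.2 to 0.6 points per region.

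**5. Chance imbalance between groups.** Assume 30% affected at 2.5 points in the same region, and 10 per group.
- SD of the number affected in one group: √(10 × 0.3 × 0.7) = 1.45.
- SD of the difference between two groups: 1.45 × √2 = 2.05.
- On the mean score: 2.05 × 2.5 / 10 = 0.51 points.
- Minimisation uses gender and grip strength only, so it does not control this directly.

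**6. Which before-value to subtract.** In the notation of step 2:
- Rating before session 1 = B, since R is then zero. Post-session score minus this = R + S, all of the soreness from the intervention.
- Rating before a later session = B + R. Post-session score minus this = S only, which drops the carry-over that the intervention caused.

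The session 1 rating is therefore the right reference. Later pre-session ratings are informative in their own right, because the current plan records nothing between the evening call and the next session.

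**7. Ratings after the change.**
- Session 1 rating only: 48 + 2 = 50 per participant.
- Rating before every session: 12 × 3 × 2 = 72 per participant, 2,160 over 30, of which 24 per participant are pre-session.

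**The case against.** The strongest reply is that this is a 30-person feasibility pilot which disclaims statistical power, that soreness is one of several descriptive measures, and that post-only ratings err on the cautious side by overstating harm rather than hiding it. That is fair as to severity. It does not remove a systematic error from a measure meant to inform the main study. The separate resistance exercise protocol cited in the text is not available here and might contain a pre-session check; even so, Appendix 3 defines the scale's times without one.

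Some stronger readings are tempting but are not supported:

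- A reader might infer that every score will be attributed to the intervention. No section says so. Existing aches can be counted in this way; it is not stated that they will be.
- A reader might infer that only severe arthritis is excluded. The words "e.g. severe arthritis, rigidity, paralysis" are examples within a wider criterion covering neuromuscular problems and other conditions that substantially affect mobility and muscle metabolism. Hip or knee replacement is also excluded, and the exercise physiologist and the general practitioner can each exclude people. Milder aches remain eligible.
- A reader might infer that nothing can adjust for differences between groups. Baseline self-reported diagnoses and medication, including over-the-counter medication, are partial proxies. Nor does the statistical section name soreness among the measures to be compared between groups, so the imbalance in step 5 concerns a comparison that the protocol does not list.
- A reader might take 0.4 to 1.2 points as the inflation of every mean. That holds only on assumed figures and with pain in both separately rated regions.

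**Conclusion.** The point stands in a limited form. The protocol plans no soreness rating before the first session or at baseline, its item does not separate causes, and every group exercises. The absolute level of soreness reported for the primary outcome and Hypothesis 2 therefore cannot be separated from background aches and may be overstated.

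The size cannot be determined from the protocol. The illustrations (3 to 12 of 30 participants with a non-zero score; 0.2 to 1.2 points on a regional mean) rest on assumed prevalence and intensity, on background pain that stays stable, and on simple addition of background and exercise soreness. The protocol sets no soreness threshold, so no stated decision can be shown to change. The correction is still worth making, because it is cheap and the value cannot be recovered later.

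**What to change.** Take the Appendix 3 arm and leg rating before the warm-up at session 1, when blood pressure is already being measured, and define it as the fixed baseline. Report the raw post-session and evening scores together with their change from that baseline, by region and by group. Keep the raw scores as a full part of the report: total soreness experienced bears directly on acceptability, and a single baseline reading reflects only one day.

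Ideally, repeat the rating before each later session and report it separately as residual soreness from the previous session. Do not make post minus pre at each session the main measure, because from session 2 onward it would subtract soreness that the intervention caused and so understate the adverse effect.

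The cost is about one minute per session and one extra CRF line, with no new instrument or staff.
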